# Comparison of the effect of hyaluronic acid injection versus extracorporeal shockwave therapy on chronic plantar fasciitis: Protocol for a randomized controlled trial

**DOI:** 10.1371/journal.pone.0250768

**Published:** 2021-06-24

## Abstract

**Background:**

Plantar fasciitis is the most common cause of pain in the plantar region of the heel, and extracorporeal shockwave therapy (ESWT) is an option used in cases where conservative treatment fails. Hyaluronic acid (HA), initially used for osteoarthrosis, is a treatment option because it has been applied to extra-articular regions, such as tendons, ligaments, and fascia. The aim of the present study will be to evaluate the outcomes of pain, function, and personal satisfaction after a single injection of HA and to compare the results with those of ESWT in patients with chronic plantar fasciitis.

**Methods:**

The study will include 80 patients who will be randomized to receive three sessions of ESWT (n = 40) or a single ultrasound-guided HA injection in the plantar fascia (n = 40). The outcomes will include the visual analog pain scale score, American Orthopaedic Foot and Ankle Society (AOFAS) score, and Foot and Ankle Outcome Score (FAOS). All of the assessments will be performed at baseline and 3, 6, and 12 months after treatment. Statistical analysis will be performed using the repeated measures ANOVA (analysis of variance test) for primary and secondary outcomes and also Fisher’s Least Significant Difference, a Post-Hoc test. We will use R software for statistical analysis, randomization, and sample size calculation.

**Results:**

Recruitment and data collection will begin in November 2020, with completion scheduled for November 2022 and final publication available in March 2023.

**Conclusion:**

This trial will evaluate the effects of a single ultrasound-guided HA injection for the treatment of chronic plantar fasciitis.

**Trial registration:**

Brazilian Clinical Trials Registry (Register Number: RBR-97vkx4) http://www.ensaiosclinicos.gov.br/rg/RBR-97vkx4/.

## Introduction

### Background

Plantar fasciitis is the most common cause of pain in the plantar region of the heel, especially in middle-aged and elderly patients [1], and is often described as an overload of the plantar fascia [2,3]. In most cases, plantar fasciitis is self-limiting, but the time for full resolution of symptoms can take up to one year, impairing the quality of life of patients and leading to frustration among the healthcare team [4].

Several treatments have been described for plantar fasciitis, and the most commonly used are noninvasive, such as nonsteroidal anti-inflammatory drugs, analgesics, night orthoses, stretching, exercises, and insoles [5].

In cases of conservative treatment failure, some studies have shown benefits of corticosteroid injection, resulting in rapid improvement and ease of progression during rehabilitation [6,7]. However, the use of corticosteroids can cause problems such as rupture of the plantar fascia, infection, atrophy of the heel pad, and even changes in skin pigmentation [8–10].

Thus, extracorporeal shockwave therapy (ESWT) has emerged as an option for recalcitrant cases of plantar fasciitis without improvement with conventional conservative treatment. This modality showed satisfactory results in a placebo-controlled study [11] but was dependent on the intensity, pulse cycle, and shockwave modality [12].

Meanwhile, due to successful treatment of knee arthrosis through hyaluronic acid (HA) injection [13], the possibility of expanding its indication for regions such as the fascia and tendons has arisen, and chronic plantar fasciitis is a possible candidate for this treatment due to its anti-inflammatory and healing potential [14,15].

### Study aim and hypotheses

The objective of the study is to compare the therapeutic efficacy of ultrasound-guided HA application for chronic plantar fasciitis with that of ESWT. We suggest that recalcitrant plantar fasciitis may benefit from the anti-inflammatory and healing properties of HA, thus accelerating the process of symptom improvement. The comparison will be with the ESWT because there are several studies proving its benefit, representing an excellent control group.

## Methods

### Study design

This study is designed as a randomized, controlled, parallel groups, and intervention trial (Fig 1).

**Fig 1 pone.0250768.g001:**
[figure not shown]
Research flow diagram.

### Recruitment

The participants will be recruited during routine orthopedic outpatient care provided by the authors at the Anália Franco and Bento Pires Unit of Prevent Senior, São Paulo, Brazil. Recruitment will be continuous and sequenced in order to select a cohort of more heterogeneous patients in the study.

### Ethics

This protocol was approved by Scientific Research Committee of Instituto Prevent Senior (Number 3,912,441–2020) and is registered on the Brazilian Clinical Trials Registry [16] (Register Number: RBR-97vkx4). The authorization to use and disclose participant information is restricted to this study, and the data will be kept for five years after publication.

### Eligibility

The inclusion criteria are as follows: 1) clinical diagnosis of plantar fasciitis with failure of conservative treatment including stretching exercises, nonsteroidal anti-inflammatory drugs, analgesics, and insoles for at least three months; 2) individuals of both genders who are older than 18 years and younger than 80 years; 3) the patient must be able to understand the informed consent form; 4) visual analog pain scale (VAS) score greater than or equal to three points (range from 0 to 10 points).

The exclusion criteria are patients with neuropathy, skin lesions, previous degenerative lesions of the ankle, previous surgeries of the ankle or Achilles tendon, previous allergy to sodium hyaluronate, or allergies to avian proteins, those less than 16 years of age, and patients with sequelae of fractures of the tibial pilon, ankle, or foot. In addition, patients with collagen disorders, rheumatoid arthritis, and seronegative arthritis will be excluded. Patients who are not recommended to use shockwave therapy include the following: patients who use anticoagulants, are pregnant, have a tumor in the treatment area, systemic infections or epilepsy.

### Handling of data

The data management plan aims to synthesize high-quality data through standardized procedures and thus, reduce errors and missing data that occur, generating an ideal database for analysis.

Patient data will be collected in order to use numbers for personal identification (ID) and managed using REDCap electronic data capture tools hosted at Instituto Prevent Senior [17,18]. Full access to the final test data of the study will be granted only to selected researchers.

REDCap (Research Electronic Data Capture) is a secure, web-based software platform designed to support data capture for research studies, providing 1) an intuitive interface for validated data capture; 2) audit trails for tracking data manipulation and export procedures; 3) automated export procedures for seamless data downloads to common statistical packages; and 4) procedures for data integration and interoperability with external sources. All data will be available to the public in a data repository, without personal identification of the participants, after publication of the study.

### Missing data

We consider minimal or no follow-up losses for the primary outcome. If more than 5% of the missing data in the primary outcome is identified, we will perform a sensitivity analysis using multiple imputations and estimation equation methods.

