### Sample size

The sample size was calculated using the *pwr* package of R software [19]. A study by Chew et al [20] was used to determine the minimum change required in the treatment of chronic plantar fasciitis with regard to the main outcome, which will consist of a change of 3.0 points in the VAS between the baseline value and that at three months of follow-up after the intervention. The pooled standard deviation was set to 4.5 after examining preliminary values. Thus, we chose a study power of 80% and type I error of 5%. The calculated sample size was 36 patients in each group, but a sample size of 40 was specified to allow loss to follow-up during the study (10%).

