### Randomization

Participants (n = 80) who meet all eligibility criteria will be randomized at a 1:1 ratio to either the HA intervention group or the control group (ESWT). Randomization will be performed in blocks (random sizes of two, four, six, and eight) and used to ensure that the treatment groups is balanced throughout the study period. This strategy ensures that the intervention group and control group are balanced regarding the number of participants. To ensure allocation concealment, random variation in block sizes (four to eight participants per block) will be used. We will use the *blockrand* package of the R software to generate the randomization table.

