### Outcome measures

The primary outcome to be evaluated will be the VAS. The questionnaire will be administered at baseline and three, six, and 12 months after the intervention during routine visits previously scheduled with the researchers.

The secondary outcomes to be evaluated will be function and personal satisfaction. The former will be assessed based on the American Orthopaedic Foot and Ankle Society (AOFAS) score [21] for the ankle and hindfoot and the Foot and Ankle Outcome Score (FAOS) [22]. The latter will be evaluated based on the personal satisfaction criteria published by Roles and Maudsley [23].

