### Statistical analysis

Statistical analysis will be conducted primarily through an intention-to-treat analysis of all patients, in both arms, except for lost cases or withdrawal of informed consent. In addition, a per–protocol analysis will be conducted.

All analysis will be performed using the statistics package of R software [19]. We will use the repeated measures ANOVA (analysis of variance test) for the primary and secondary outcomes and also the Fisher’s Least Significant Difference, a Post-Hoc test.

Continuous variables will be measured using descriptive statistics, including the mean and standard deviation, and tested for the normality of their distribution using the Shapiro test [24]. Categorical variables will be presented according to their proportion and confidence interval.

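### As normally run, the only planned missing-data sensitivity analysis cannot show bias when loss before month 3 depends on unseen pain; add a delta-shifted imputation with a tipping point.

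*Protocol article*

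**What the plan says.** All of the following comes from the protocol article.

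- **Outcome measures:** the primary outcome is VAS, and "The questionnaire will be administered at baseline and three, six, and 12 months after the intervention". No VAS visit falls between baseline and month 3.
- **Sample size:** the calculation rests on "a change of 3.0 points in the VAS between the baseline value and that at three months of follow-up after the intervention". It adds: "The calculated sample size was 36 patients in each group, but a sample size of 40 was specified to allow loss to follow-up". The stated allowance is 10%.
- **Statistical analysis:** the main analysis is called intention-to-treat and covers patients "in both arms, except for lost cases or withdrawal of informed consent". In effect it is a completer analysis, by repeated measures ANOVA.
- **Missing data:** little or no loss is expected. If more than 5% of the primary outcome is missing, "we will perform a sensitivity analysis using multiple imputations and estimation equation methods". The variables in the imputation, the missingness assumption and any weighting are not given.
- **Abstract, Methods:** VAS, AOFAS and FAOS are all assessed at baseline, so VAS is not the only baseline predictor available.

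**The concern.** Because the main analysis drops lost cases, the sensitivity analysis is the only stated check on what their absence does to the result. Such a check should vary the assumption that the data cannot test, namely that leavers fare like similar stayers. Multiple imputation in its usual form assumes missing at random. Unweighted estimating equations assume loss that is completely at random or depends only on modelled covariates. Neither departs from that assumption, and for a patient with no follow-up VAS there is nothing after baseline to correct it.

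Loss related to outcome is plausible in this trial. The Background calls the condition self-limiting in most cases, so recovered patients may stop attending. Those enrolled have already failed conservative treatment, so patients without benefit may seek care elsewhere. Visit burden also differs by arm: one injection against three weekly sessions. If the main and sensitivity analyses agreed, a reader could take that as robustness although the methods share the untested assumption.

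**Working it through.** **1. The plan's own figure.** Inputs from Sample size: difference 3.0, SD 4.5, power 80%, type I error 5% (two-sided assumed, since the article does not say).

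n per group = 2 x (1.960 + 0.842)^2 x 4.5^2 / 3.0^2 = 2 x 7.851 x 2.25 = 35.3, so 36. The t-test version gives 36.3, with power 79.7% at 36. Then 36 / (1 - 0.10) = 40. The stated 36 and 40 are reproduced.

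**2. Would the analysis be triggered?** Trigger: 0.05 x 80 = 4 patients. Planned loss: 0.10 x 80 = 8 patients. At the trial's own allowance the sensitivity analysis would run, if the 5% is counted in patients. The 10% covers the whole study, so only part of it need fall before month 3.

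**3. What informs each kind of missing value**

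| Patient | Data available | What the named methods can do |
|---|---|---|
| Lost before month 3 | Baseline VAS, AOFAS, FAOS | Predict from comparable stayers only |
| Misses month 3, returns later | Baseline plus month 6 or 12 | Use later VAS |
| Lost after month 3 | Baseline plus month 3, perhaps month 6 | Use observed follow-up VAS |

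The gap is confined to the first row.

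**4. Size of what stays hidden.** Let p be the proportion lost before month 3 in an arm, and D the amount by which the leavers' true month-3 VAS exceeds the value imputed for them.

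Hidden bias in the arm difference = p1 x D1 - p2 x D2

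The p and D values below are assumptions; the article gives none by arm.

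- 15% against 5%, D = 2 in both: 0.15 x 2 - 0.05 x 2 = 0.20
- 10% in each arm, D = 3 in one and 0 in the other: 0.10 x 3 = 0.30
- 20% against 0%, D = 3: 0.20 x 3 = 0.60
- 10% in each arm, D = 2 in both: 0.20 - 0.20 = 0

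For scale, the standard error at the stated SD is 4.5 x sqrt(2/36) = 1.06. So 0.20 is about 0.2 standard errors and 0.60 about 0.6.

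**5. Simulation of the mechanism.** Setting: 200,000 per arm, no true difference, 10% lost before month 3 in each arm, selective loss in one arm only. Assumed: VAS SD 2.5, baseline to month-3 correlation 0.3 or 0.6, function score to month-3 correlation 0.4, log-odds slope of loss 1.5 per SD. Entries are the estimated month-3 difference at correlation 0.3 / 0.6; the true value is 0. MI is multiple imputation.

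| Loss depends on | Completers, month-3 VAS | Completers, change | Baseline-adjusted completers | MI with baseline VAS | MI adding function score |
|---|---|---|---|---|---|
| Baseline VAS | -0.10 / -0.17 | +0.20 / +0.13 | -0.01 / +0.01 | -0.01 / +0.01 | -0.01 / +0.01 |
| Baseline function score | -0.12 / -0.13 | -0.11 / -0.13 | -0.12 / -0.13 | -0.12 / -0.13 | 0.00 / 0.00 |
| Unseen month-3 VAS | -0.30 / -0.31 | -0.21 / -0.12 | -0.28 / -0.20 | -0.28 / -0.20 | -0.23 / -0.16 |

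The first two rows show imputation removing bias when the relevant baseline variable is in the model. In the third row it matches the baseline-adjusted completer analysis, and a further baseline score leaves most of the bias. This agrees with step 4: 0.28 / 0.10 = 2.8 and 0.20 / 0.10 = 2.0 points for D.

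Estimating equations were not simulated; the statement about them rests on their usual assumptions.

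**The case against.** The strongest case against the point has four parts.

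- **The article does not fix the imputation model.** Predictors, missingness assumption and weights are details that an article commonly leaves to a full protocol or analysis plan. Delta adjustment is itself a form of multiple imputation, so nothing in the Missing data section excludes it. This stands: the section is not wrong, and the point is an improvement to a stated method.
- **The named methods do useful work.** A reader might infer that they simply hand back the completer result, that they can reveal no bias from loss, and that they should be replaced. The documents do not support that. AOFAS and FAOS are collected at baseline with VAS, and imputation using them corrects loss driven by those variables. VAS at months 3, 6 and 12 informs patients lost later or absent once, whom the main analysis may discard. Unweighted estimating equations also tolerate loss that depends on modelled covariates, so there is no ground for dropping them.
- **The effect is small and the inputs are assumed.** Loss rates by arm and shifts appear nowhere in the article, and equal loss with equal shift gives no bias. This stands and limits the weight of the point.
- **How agreement would be reported is unknown.** This also stands; the article does not say.

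None of this answers the remaining gap: no named analysis departs from the assumption that leavers resemble comparable stayers.

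**Conclusion.** The point holds in a limited form. For patients lost before month 3, multiple imputation and estimating equations as normally run largely repeat a baseline-adjusted completer analysis. They cannot reveal bias from loss that depends on unobserved pain.

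The hidden bias is each arm's loss proportion times its shift, differenced between arms: 0.20 to 0.60 VAS points in the unbalanced examples, against 3.0 in the sample size calculation, and nil when loss and shift are equal. These sizes rest on assumed loss rates and shifts, and the simulated ones also on assumed SD, correlations and loss mechanism. That the methods miss outcome-dependent loss does not depend on those values. It does depend on the methods being run in their usual form, which the article neither states nor rules out.

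This is a cheap improvement to a stated analysis and does not undermine the design.

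**What to change.** Keep both named analyses and add to the Missing data section:

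1. Impute month-3 VAS by arm from baseline VAS, AOFAS and FAOS, and any later VAS.
2. Shift the imputed values of lost patients by 0, 1, 2 and 3 points, in both directions and separately in the HA and ESWT arms. That is 7 shifts per arm and 7 x 7 = 49 combinations; zero in both arms is standard imputation.
3. Report the tipping point at which the conclusion changes, or state that none is reached within the grid.

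The cost is a sentence or two of text and a short loop around the imputation already planned. No new data or visits are needed.

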### Sample size

The sample size was calculated using the *pwr* package of R software [19]. A study by Chew et al [20] was used to determine the minimum change required in the treatment of chronic plantar fasciitis with regard to the main outcome, which will consist of a change of 3.0 points in the VAS between the baseline value and that at three months of follow-up after the intervention. The pooled standard deviation was set to 4.5 after examining preliminary values. Thus, we chose a study power of 80% and type I error of 5%. The calculated sample size was 36 patients in each group, but a sample size of 40 was specified to allow loss to follow-up during the study (10%).

### Randomization

Participants (n = 80) who meet all eligibility criteria will be randomized at a 1:1 ratio to either the HA intervention group or the control group (ESWT). Randomization will be performed in blocks (random sizes of two, four, six, and eight) and used to ensure that the treatment groups is balanced throughout the study period. This strategy ensures that the intervention group and control group are balanced regarding the number of participants. To ensure allocation concealment, random variation in block sizes (four to eight participants per block) will be used. We will use the *blockrand* package of the R software to generate the randomization table.

### Intervention

The interventions will be performed in the authors’ outpatient clinic and only after the participants sign the informed consent form and are allocated to one of the study arms.

The intervention with HA will be performed by the author ([name]) through a single application of Ostenil Plus^®^ (2.0 mL with 40 mg of 2.0% sodium hyaluronate, TRB Chemedica, Munich, Germany). This product is indicated for extra-articular regions, as indicated in the package insert: “It is also indicated in cases of pain and mobility restriction due to inflammation and degeneration in tendons, tendon sheaths, and entheses.” This product contains low-molecular-weight HA. The injection will be guided in all cases by a portable ultrasound Butterfly iQ^®^ device (Butterfly Network, New York, USA) to increase the precision and efficacy of the intervention.

The ESWT intervention (radial type) will be performed by the author ([name]) in three sessions in total, one per week, using a Swiss DolorClast Master^®^ device (Electro Medical System, Nyon, Switzerland). Patients will be subjected to 2,500 focused shockwaves with an energy flux density of 0.05 mJ/mm^2^ and a frequency of 8 Hz. Each session will last approximately 15 min. The treatment will follow that recommended by the generator’s distribution company.

After the interventions, participants will be recommended to perform daily posterior chain stretching exercises while remaining under follow-up with the physical therapy team. The use of oral analgesics will be prescribed and authorized.

Regarding the risks of the interventions, local injection of HA may cause adverse effects such as pain, sensation of heat, redness, and edema, as described in the package insert. Shockwave therapy may cause an inflammatory process and local pain, but these symptoms are usually quickly resolved with mild analgesics.

### Measures

Clinical evaluation using pain, function, and personal satisfaction scores will be performed for a period of one year in the following intervals after the interventions: three, six, and 12 months. Thus, we will be able to evaluate the results in the short, medium, and long term. The authors (X.X.X.X., X.X.X.) will blindly evaluate the participants regarding the intervention performed.

### Outcome measures

The primary outcome to be evaluated will be the VAS. The questionnaire will be administered at baseline and three, six, and 12 months after the intervention during routine visits previously scheduled with the researchers.

The secondary outcomes to be evaluated will be function and personal satisfaction. The former will be assessed based on the American Orthopaedic Foot and Ankle Society (AOFAS) score [21] for the ankle and hindfoot and the Foot and Ankle Outcome Score (FAOS) [22]. The latter will be evaluated based on the personal satisfaction criteria published by Roles and Maudsley [23].

### Statistical analysis

Statistical analysis will be conducted primarily through an intention-to-treat analysis of all patients, in both arms, except for lost cases or withdrawal of informed consent. In addition, a per–protocol analysis will be conducted.

All analysis will be performed using the statistics package of R software [19]. We will use the repeated measures ANOVA (analysis of variance test) for the primary and secondary outcomes and also the Fisher’s Least Significant Difference, a Post-Hoc test.

Continuous variables will be measured using descriptive statistics, including the mean and standard deviation, and tested for the normality of their distribution using the Shapiro test [24]. Categorical variables will be presented according to their proportion and confidence interval.

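### The primary analysis is labelled intention-to-treat but leaves out lost and withdrawn patients, so its estimate is open to attrition bias

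*Protocol article*

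**What the plan says.** The Statistical analysis section of the protocol article defines the main analysis as an "intention-to-treat analysis of all patients, in both arms, except for lost cases or withdrawal of informed consent". It then says: "In addition, a per–protocol analysis will be conducted". On the model it says: "We will use the repeated measures ANOVA (analysis of variance test) for the primary and secondary outcomes". According to Outcome measures, VAS is recorded at baseline and at 3, 6 and 12 months.

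The Missing data section opens with an expectation: "We consider minimal or no follow-up losses for the primary outcome". If more than 5% is missing for the primary outcome, "we will perform a sensitivity analysis using multiple imputations and estimation equation methods".

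The Sample size section bases the calculation on "a change of 3.0 points in the VAS between the baseline value and that at three months of follow-up". It obtains 36 per group and raises this to 40 to cover 10% loss over the study.

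**The concern.** The label and the definition disagree. Intention-to-treat keeps every randomised patient in the assigned arm; this set drops patients because of events after randomisation. This is a statement made in the document, not a detail left to an analysis plan that is not shown. An analysis plan that follows it inherits the error, and one that departs from it contradicts the published protocol.

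What is at stake is the protection that randomisation gives to the primary comparison. One arm has a single injection and the other three weekly shockwave sessions. The Measures section describes blinding of the evaluators only, and pain is the patient's own report. Loss because pain persists, because it has resolved, or because the treatment is a burden could plausibly differ between arms.

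The named model may make matters worse. In its classical form, repeated measures ANOVA uses only patients with every visit. A patient seen at 3 months and missing at 12 would then lose the value at the time point on which the trial is sized.

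**Working it through.** **Inputs from the Sample size section:** difference 3.0 points, SD 4.5, power 80%, type I error 5%, 36 per group raised to 40 for 10% loss. Sidedness is not stated. The 3.0 points are taken here as a between-group difference, because that reading reproduces the plan's figure.

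**Step 1. Reproduce the plan's figure.**
- Per group: n = 2 × (1.960 + 0.842)² × (4.5/3.0)² = 2 × 7.85 × 2.25 = 35.3, rounded up to 36. The exact noncentral-t calculation gives 37.
- A one-sided test would give 28 and a paired test 20, so the stated 36 is a two-sided, two-sample comparison.
- Loss allowance: 36 / (1 − 0.10) = 40. Both stated figures reproduce.

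**Step 2. Power when lost patients are dropped** (exact t, difference 3.0, SD 4.5; loss above 10% is an assumption).

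| Loss | Analysed per arm | Power |
|---|---|---|
| 0% | 40 | 83.8% |
| 10% (planned) | 36 | 79.7% |
| 15% | 34 | 77.3% |
| 20% | 32 | 74.7% |
| 30% | 28 | 68.8% |

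By the normal approximation, the first two rows are 84.7% and 80.7%. At the planned loss, the exclusion leaves the trial at its design target.

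**Step 3. Bias from dropping patients.** Let C be the mean improvement of the patients kept in an arm, d the fraction dropped, and x the number of points by which dropped patients improve less (assumption). The mean of the whole arm is (1 − d) × C + d × (C − x) = C − d × x, so the analysed mean is too favourable by d × x. The bias in the group difference is (difference in loss rates) × x, if x is the same in both arms.
- 5% versus 15% loss, x = 1 to 3: 0.10 × 1 to 0.10 × 3 = 0.1 to 0.3 points.
- 0% versus 20% loss, x = 1 to 3: 0.2 to 0.6 points.
- Equal loss and equal x: 0.

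**Step 4. Cost of discarding partly followed patients** (assumed loss of 5% by month 3 and 15% by month 12; complete-case ANOVA).
- With a 3-month VAS: 38 per arm, power 81.8%.
- Complete at all visits: 34 per arm, power 77.3%.

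**Step 5. Does the planned safeguard reach the primary estimate?** If the 5% trigger counts patients, it is passed when more than 4 of 80 are lost (0.05 × 80 = 4). With 10% loss, Binomial(80, 0.10) gives P(more than 4) = 0.912. The sensitivity analyses would then very probably run, but the primary estimate would still come from the reduced set.

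**The case against.** The strongest reply is that the plan has already provided for loss. It budgets 10%, and it names two methods for missing data. Estimating equations can use every observed visit, which is close to the remedy proposed here. At the planned loss, the 5% trigger would almost certainly be met. All of this stands and softens the point. It does not remove it, because both methods are sensitivity analyses and the primary estimate stays the same.

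Three stronger readings are tempting, and the document does not support them.
- *The exclusion takes power well below target.* A reader might apply 10% loss independently to each of three visits: 0.9³ = 0.729, about 29 per arm, power 70.4%. The Sample size section gives 10% for the whole study, whereas this implies 27%, nearly three times as much. At the plan's own figure, power is 79.7%.
- *Every partly followed patient is deleted.* Who counts as a lost case is not defined, and the text does not say that the ANOVA is the complete-case form. The loss of 3-month values is therefore conditional on that form.
- *The Missing data and Sample size sections contradict each other.* One states an expectation and the other a contingency. Expecting little loss while budgeting for 10% is ordinary prudence.

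It can also fairly be said that the illustrated bias is small: 0.3 points is one tenth of the 3.0-point planning difference, and the bias vanishes when loss and deficit are equal in the two arms. In addition, a mixed model recovers little from a patient with no follow-up VAS, and data from a patient who withdraws can be used only as far as consent permits.

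**Conclusion.** The point holds as a mislabelled primary analysis set that leaves the primary estimate open to attrition bias. Bias arises if loss is related to outcome and the effect of that loss differs by arm. Under the assumed figures it is 0.1 to 0.3 VAS points at 5% versus 15% loss and 0.2 to 0.6 at 0% versus 20%; it can also be zero. The document gives no loss rates by arm and no outcome gap for lost patients, so these figures are illustrations and not forecasts.

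Discarding observed 3-month values is a second consequence, if the ANOVA is run on complete cases. Power is secondary: it falls clearly below target only if complete-case loss exceeds the 10% allowed.

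**What to change.** - Define the primary set as all randomised patients in their assigned arm, and remove the exception for lost patients. For withdrawals, keep data collected before withdrawal where consent allows.
- Analyse all observed VAS values with a likelihood-based mixed model for repeated measures in place of repeated measures ANOVA, so that a patient who misses a later visit still contributes the 3-month value.
- Run the missing-data sensitivity analysis whatever the missing rate. This also covers patients with no follow-up VAS, for whom the mixed model adds little.
- If the reduced set is kept, label it a completer analysis.

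The cost is a change of wording, a standard mixed-model fit in R and a little more analysis work. No new patients, visits or measurements are needed. The change should be settled before any comparison by arm is seen, because it decides who counts in the primary comparison.

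### The trial is sized on the 3-month VAS change, but the planned repeated measures ANOVA does not say which effect or contrast is the primary test

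*Protocol article*

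**What the plan says.** Three sections of the protocol article bear on the primary test.

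- **Sample size.** The main outcome is "a change of 3.0 points in the VAS between the baseline value and that at three months of follow-up after the intervention". Power is set at 80% and type I error at 5%. On the spread, the section says "The pooled standard deviation was set to 4.5 after examining preliminary values". Its result reads "The calculated sample size was 36 patients in each group", raised to 40 for 10% loss.
- **Outcome measures.** "The primary outcome to be evaluated will be the VAS", collected at baseline, 3, 6 and 12 months. This section singles out no time point.
- **Statistical analysis** (and the abstract's Methods). "We will use the repeated measures ANOVA (analysis of variance test) for the primary and secondary outcomes". The same sentence adds Fisher's LSD as a post-hoc test. It names no ANOVA effect, visit contrast or covariate.

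The Study aim section expects HA to help by "thus accelerating the process of symptom improvement".

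**The concern.** The sample size answers one question: do the arms differ in VAS change at three months? The analysis section names a method that yields several tests: a group main effect, a group-by-time interaction, and a set of pairwise comparisons. None is designated as primary, and neither omnibus test is the contrast on which the trial was sized.

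Two things are at stake. A significant omnibus result could be reported as a positive trial without showing anything at three months. And with several candidate tests and none named, the one that carries the conclusion can be picked after the data are seen.

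**Working it through.** **1. Reproduce the plan's figure.** Inputs from Sample size: difference 3.0, SD 4.5, power 80%, two-sided 5% (sidedness is not stated; one-sided gives 28). n per group = 2 × [4.5 × (1.960 + 0.842) / 3.0]² = 35.3, so 36. With 10% loss, 36 / 0.9 = 40. The t-test version gives 36.3. The stated size therefore belongs to a two-sample comparison of the 3-month change, with power about 80% at 36 per group.

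**2. Assumptions for the rest.** All four visits enter the ANOVA. This is the natural reading, though not stated outright. Variance is equal at every visit, with a common between-visit correlation ρ of 0.3, 0.5 or 0.7; the protocol gives none. It also does not say whether 4.5 is the SD of change or of the VAS level, so both readings are shown. With σ the level SD, SD of change = σ√[2(1 − ρ)]; the two readings coincide at ρ = 0.5.

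**3. Group-by-time interaction.** With between-group differences d_k at the four visits and mean d̄, the noncentrality is λ = (n/2) Σ(d_k − d̄)² / [σ²(1 − ρ)], on 3 and 210 df. If 4.5 is the SD of change, σ²(1 − ρ) = 4.5²/2 = 10.125 at every ρ.

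- Difference at 3 months only, (0, 3, 0, 0): Σ = 6.75, λ = 18 × 6.75 / 10.125 = 12.0, power 83%.
- Difference at 12 months only, (0, 0, 0, 3): Σ = 6.75, λ = 12.0, power 83%. The 3-month change test stays at 5%.
- Fading difference, (0, 3, 1.5, 0): Σ = 6.19, λ = 11.0, power about 80%.

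The first two patterns give the same λ, so the test cannot tell them apart. If 4.5 is the level SD, the 12-month-only figure runs from about 68% (ρ = 0.3) to 97% (ρ = 0.7).

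**4. Group main effect.** SE = √[2σ²(1 + 3ρ)/(4n)]. For the fading pattern the mean difference is (0 + 3 + 1.5 + 0)/4 = 1.125.

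| ρ | SE, 4.5 = level SD | power | SE, 4.5 = SD of change | power |
|---|---|---|---|---|
| 0.3 | 0.731 | 33% | 0.618 | 44% |
| 0.5 | 0.839 | 26% | 0.839 | 26% |
| 0.7 | 0.934 | 22% | 1.205 | 15% |

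**5. LSD comparisons.** Three independent 5% tests at 3, 6 and 12 months give 1 − 0.95³ = 14.3%. Simulation with correlated visits gives 14.2%, 12.5% and 11.0% at ρ = 0.3, 0.5 and 0.7 when there is no effect and no omnibus test is required first.

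**6. Baseline-adjusted 3-month contrast.** Residual SD is 4.5√[(1 + ρ)/2] if 4.5 is the SD of change, and 4.5√(1 − ρ²) if it is the level SD. Power at 36 per group:

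| ρ | SD of change: adjusted / unadjusted change | Level SD: adjusted / unadjusted change |
|---|---|---|
| 0.3 | 93% / 80% | 83% / 66% |
| 0.5 | 90% / 80% | 90% / 80% |
| 0.7 | 86% / 80% | 97% / 95% |

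**The case against.** The best reply is that the protocol does provide a route to three months. Sample size names the time point, Outcome measures merely lists when the questionnaire is given, and Fisher's LSD after the ANOVA can show at which visit, and in which direction, the arms differ. If LSD is run only after a significant interaction, the false-positive chance under no effect cannot exceed the interaction's own 5%, so the 11% to 14% applies only without that gate. Much of this stands. What does not is the inference that the primary test is therefore fixed: the LSD comparisons are unnamed and post hoc, no gate is stated, and as usually run they compare levels rather than the change used for sizing.

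A reader might also draw stronger conclusions that the protocol does not support:

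- **That the planned analysis is underpowered.** The low figures belong to a group main effect that the protocol never names as primary. The interaction roughly matches the change test in power. The fading pattern is itself inferred from the stated hypothesis; the Measures section also wants medium- and long-term results.
- **That leaving out baseline VAS as a covariate biases the comparison.** Randomisation protects against that, and an ANOVA with baseline as a repeated level already uses baseline through the interaction. On its own, the covariate could be left to an analysis plan not shown here.
- **That the adjusted contrast always has the most power.** With a constant effect and ρ = 0.3, the main effect does slightly better: 86% against 83% with 4.5 as the level SD, and 95% against 93% as the SD of change.

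**Conclusion.** The point holds as a mismatch between the sizing and the stated analysis. The protocol fixes a powered question at three months and a named method, and nothing connects them. This is more than a detail left to a fuller plan, because a positive ANOVA need not answer the question the trial was sized for: the interaction is as likely to be significant for a difference confined to 12 months as for one confined to 3 months (about 83% each if 4.5 is the SD of change).

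The secondary sizes are conditional. The main effect's low power matters only if that effect is used and the benefit fades. The LSD error rate applies only to ungated, unadjusted testing. All power figures assume 36 per arm, a common between-visit correlation of 0.3 to 0.7 and equal variances.

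**What to change.** In Statistical analysis, name one primary test: the HA-minus-ESWT difference in VAS at 3 months, with 95% CI, adjusted for baseline VAS. Estimate it by ANCOVA, or as the 3-month contrast of a mixed model on the 3-, 6- and 12-month values. Report 6 and 12 months as secondary, from the same model if the mixed model is used. Repeat the 3-month time point in Outcome measures, and state in Sample size whether 4.5 is the SD of change or of the level.

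No new data are needed, since baseline VAS is already collected. If 4.5 is the SD of change, the existing size gives about 86% to 93% power, against 80% unadjusted.

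The cost is small but not nil. The Results section says recruitment began in November 2020, so the change needs a dated amendment before anyone sees unblinded data, and the later visits are explicitly given secondary status.
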